#### Data collected at 3 months after informed consent provided

1. Life events after accidental injury

2. Outpatient or inpatient treatment

3. Physical examination: Performance status, blood pressure at rest (right hand), heart rate, laboratory data

4. Psychiatric evaluation: MINI [65,66], CAPS [52,53], MADRS [63,64]

5. Psychological responses: IES-R, HADS, SF-36, CD-RISC [56], BAQ [57]

6. Physiological assessment

7. Whole blood and serum

8. Adverse events

9. Number of days of leave from work taken from the time of injury

### Reporting of adverse events and protection of participants

An adverse event is defined as any unwanted or unintended sign, symptom, or disease seen in trial participants, regardless of the causal relationship with the study interventions. After enrollment, patients undergo a short physical examination and then complete the questionnaires and interviews. Safety issues concerning omega-3 fatty acid supplementation, including monitoring of vital signs and records of adverse events, are investigated at least twice a week during hospitalization. After discharge, safety issues are checked by telephone or email contact. When an adverse event is suspected, researchers and clinical research coordinators evaluate and record the event. Based on the following criteria, adverse events are evaluated for severity according to the following three levels.

1. Mild: Some symptoms or signs observed, but the participant can continue the trial without treatment.

2. Moderate: Some symptoms or signs observed, but the participant can continue the trial with treatment, such as reducing the dose of the test capsules or administering drugs.

3. Severe: Clinical status and daily activities are significantly affected, and discontinuation of the test capsules may be needed. Examples include headache, diarrhea, soft stool, and belching that are severe enough to reduce daily activities.

An association between the adverse event and test capsules is evaluated on four levels based on the following criteria. If it is judged there is “No association,” the reason for the judgment is also explained in the report.

1. Not related: Symptoms can be clearly explained by factors other than the test capsules.

2. Possibly related: Although the symptoms can be considered to be caused by factors other than the test capsules, a possible relationship between them cannot completely be ruled out.

3. Probably related: The symptoms are unlikely to be caused by factors other than the test capsules.

4. Related: Causal relationship with the test capsules is strongly suspected, due to a temporal relationship between test capsule administration and occurrence of the adverse event, a correlation between the dose of the test capsules and symptom severity, or when occurrence of the adverse event cannot be explained by factors other than the test capsules.

### Failure to attend a hospital visit or failure to reach the participant or family

If a participant does not visit the hospital for a follow-up appointment, the clinical research coordinator calls the participant or their family and encourages a visit soon after confirming the reason for not visiting. If visiting is judged to be difficult, a phone interview is conducted instead. When contacting the participant, the coordinator confirms that the person talking over the phone is the participant himself or herself. When mailing materials, a confidential form is used to protect personal information.

### Outcomes

#### Primary outcome

Total score of the CAPS-DX at 3 months follow-up.

#### Secondary outcomes

1. Incidence of diagnosis of PTSD (full PTSD and partial PTSD) at 1 and 3 months follow-up

2. Total score of the CAPS-DX at 1 month follow-up

3. MADRS score at 1 and 3 months follow-up

4. Incidence of diagnosis of major depressive disorder evaluated by MINI at 1 and 3 months follow-up

5. Physiological response to script-driven imagery and audiovisual stimuli at 3 months follow-up

6. IES-R score at 1 and 3 months follow-up

7. HADS score at 1 and 3 months follow-up

8. SF-36 score at 1 and 3 months follow-up

9. CD-RISC score at baseline and 3 months follow-up

10. BAQ score at baseline and 3 months follow-up

11. Serum BDNF at baseline and 1 and 3 months follow-up

12. Number of days of leave from work taken from the time of injury

13. Dehydroepiandrosterone at 1 and 3 months follow-up

14. Neuropeptide Y at 1 and 3 months follow-up

15. Interleukin 1 beta at 1 and 3 months follow-up

16. Interleukin 6 at 1 and 3 months follow-up

17. Tumor necrosis factor alpha at 1 and 3 months follow-up

18. D-serine at 1 and 3 months follow-up

19. L-serine at 1 and 3 months follow-up

20. DL-serine at 1 and 3 months follow-up

21. Activin at 1 and 3 months follow-up

### Statistical analyses

All analyses are conducted according to the intention-to-treat principle.

#### Primary analysis

The primary purpose of this trial is to examine whether patients receiving omega-3 fatty acid supplementation after physical trauma score on average 10 points lower on the CAP scale at 3 months follow-up than those receiving placebo. Using analysis of covariance, mean score differences, 95% confidence intervals, and P values are calculated. Two-tailed tests will be used, and the α level will be set at 5%. If background factors are found that may influence prognosis even if the assignment code is blinded, those factors will be entered as covariates in the analysis.

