### Randomization

An independent statistician ([name]) composed tables of block randomization with three stratification factors using a computer-generated random allocation sequence. Stratification factors included sex, age (<40 or ≥40 years), and sense of life threat. This resulted in eight (2×2×2) different stratified tables of supplement numbers. Those tables were sent to an independent pharmacist ([name]); he securely kept the tables and prepared numbered supplements bottles according to the tables. Both the research team and participants will be blinded to randomization until the last participant has completed the protocol and the spreadsheets of all results are finalized. Stratification by sex, age, and sense of life threat has been justified by previous studies; the prevalence of PTSD and major depressive disorder were higher in women than in men [43,44]; and our previous cohort study of MVA survivors showed that sense of life threat was a strong predictor of subsequent PTSD [9]. Moreover, according to the National Health and Nutrition Survey on food group consumption by age group, the amount of meat products consumed such as pork and beef is higher for both sexes before age 40, but after this age the amount of seafood consumption increases. Also omega 3 fatty acid contents in red blood cells increase with age in the Japan population [45].

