#### Erythrocytes for fatty acid analysis

Seven milliliters of whole blood are obtained with ethylene-diamine tetraacetic acid in the emergency room (before ICU admission, baseline) and at the 3-month assessment for determination of fatty acids. Erythrocytes are washed twice with saline and frozen at −80°C until analysis. Total lipids are extracted according to the method of Bligh and Dyer [61]. Total phospholipid fractions are separated by thin-layer chromatography. After transmethylation with HCl–methanol, the fatty acid composition is analyzed by gas chromatography (GC-2014 Shimadzu Corporation, Kyoto, Japan) equipped with a DB-225 capillary column (length, 30 m; internal diameter, 0.25 mm; film 0.25 μm; J&M Scientific, Folsom, CA). The entire system is controlled using the gas chromatography software GC-solution version 2.3 (Shimadzu Corporation, Kyoto, Japan).

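### The primary ANCOVA leaves its covariates to a rule of adding factors if they are found to matter, when it could simply fix the three factors that the randomization is stratified by

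*Protocol article*

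**What the plan says.** The primary outcome is "Total score of the CAPS-DX at 3 months follow-up". Under Primary analysis the protocol article states: "Using analysis of covariance, mean score differences, 95% confidence intervals, and P values are calculated". It then gives its one rule on covariates: "If background factors are found that may influence prognosis even if the assignment code is blinded, those factors will be entered as covariates". That rule has no candidate list, no criterion for counting as found, and no time point.

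Under Randomization the article describes "block randomization with three stratification factors using a computer-generated random allocation sequence". It lists them: "Stratification factors included sex, age (<40 or ≥40 years), and sense of life threat". Sex is justified by the higher prevalence of PTSD and major depression in women. For life threat, the group's own cohort showed that "sense of life threat was a strong predictor of subsequent PTSD". Age is justified by diet and by omega-3 content of red cells, not by PTSD risk. Neither section says whether the stratifiers enter the primary model.

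Table 1 schedules CAPS only at 1 and 3 months, so there is no baseline CAPS to serve as the default covariate.

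**The concern.** An ANCOVA with no covariates fixed is not yet a model. Two analysts who both follow the Primary analysis section could fit different models and report different primary P values.

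The obvious covariates are those the trial randomizes by. Stratified blocks remove part of the between-arm variation that prognostic strata would otherwise cause. An analysis that omits the strata still counts that variation in its standard error, so the interval is wider than the design warrants and some power is lost. If factors are instead chosen because they look prognostic in the trial data, the content of the only confirmatory test rests on judgement. These are largely alternative harms: the first arises if the stratifiers are left out, the second if the rule is used to bring factors in.

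**Working it through.** **Inputs from the protocol article.** Difference 10 points, SD 15, two-sided α 0.05, power 90%, dropout about 30%, 49 analysed and 70 randomized per group (Estimation of sample size); eight strata (Randomization).

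**Assumptions.** R², the share of 3-month CAPS variance explained by the three stratifiers, is not given; I take 5% to 20%. Block size is not given; the simulations use 4. Dropout is taken as random.

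**The plan's own figure.** 2 × [15 × (1.960 + 1.282) / 10]² = 47.3, so 48 per arm; the two-sample t version gives 48.3, so 49. Then 49 / 0.70 = 70 per arm, 140 in total. The stated size reproduces. It assumes no covariate gain, so this point does not affect it.

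**Stratifiers left out, strata exactly balanced.** True SE = model SE × √(1 − R²). The unadjusted SE is therefore too large by the factor 1/√(1 − R²), and type I error is 2 × [1 − Φ(1.96/√(1 − R²))].

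**Stratifiers left out, 30% random dropout.** Losing 30% at random restores about 30% of the between-stratum variation between arms. The true variance is then roughly (1 − R²) + 0.3R² = 1 − 0.7R² of the model variance, and 1 − 0.7R² replaces 1 − R² in both formulas.

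| Assumed R² | SE excess, exact balance | SE excess, 30% dropout | Type I, exact balance | Type I, 30% dropout |
|---|---|---|---|---|
| 5% | 2.6% | 1.8% | 4.4% | 4.6% |
| 10% | 5.4% | 3.7% | 3.9% | 4.2% |
| 20% | 11.8% | 7.8% | 2.8% | 3.5% |

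The dropout columns are the realistic ones. Simulation with 140 randomized, eight strata and 30% dropout gives an SE about 2% to 8% too large and type I error about 4.8% to 3.4%. Separate runs agree within a few tenths of a percentage point.

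**Power at 49 per arm.** The unadjusted model SE is 15 × √(2/49) = 3.03, and 10/3.03 = 3.30.
- Unadjusted, with dropout: Φ[(3.30 − 1.96)/√(1 − 0.7R²)] = 91.4%, 91.8% and 92.6% for R² of 5%, 10% and 20%.
- Adjusted: Φ[3.30/√(1 − R²) − 1.96] = 92.3%, 93.6% and 95.8%.
- Loss: 0.9, 1.8 and 3.2 points. Simulation at R² = 20% gives 91.8% against 94.9%, about 3 points.

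**Interval width at 49 per arm.** The unadjusted 95% half-width is 1.96 × 3.03 = 5.94 points. With the stratifiers it is 5.79 (R² = 5%) to 5.31 (R² = 20%), a difference of 0.15 to 0.63 CAPS points.

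**Factors admitted by the rule while blinded.** I read the rule as keeping a candidate if p < 0.10 against the outcome, with the three stratifiers and 12 pure-noise covariates as candidates. In 4,000 simulated trials per setting, for R² from 0 to 30%, type I error was 4.9% to 5.0%. At R² = 20% the mean SE was 2.71, against 2.73 with the stratifiers fixed in advance and 3.03 unadjusted.

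**The case against.** The strongest reply is that silence is not exclusion. This is a condensed article, and a full covariate list is commonly left to the analysis plan. The rule admits factors that may influence prognosis, and the article already calls life threat a strong predictor, so the rule could well bring it in; the simulation shows that the lost precision then returns. This stands against any claim that the interval will certainly be too wide. It does not remove the point: the article does state a covariate rule for its confirmatory test, and a plan that fixed the model would have to replace that sentence, not merely add detail.

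A reader might also infer that the model is chosen after the data are in, with a false-positive risk. The documents do not support that. No time of selection is stated, the sentence itself refers to a blinded code, and blinded selection holds type I error near 5%. Picking the smallest P value unblinded would raise it to about 7% to 8% in simulation, but the article describes no such procedure.

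A further temptation is to say that erythrocyte fatty acids, taken "at the 3-month assessment for determination of fatty acids", would reveal the arms to whoever picks covariates. That is speculative. The Informed consent section places sample analyses after completion of all clinical trials, telephone follow-up yields no blood, these fatty acids are not among the listed outcomes, and nothing says that the person choosing covariates sees them.

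**Conclusion.** The point holds in a modest form. The covariate set of the primary ANCOVA is badly fixed, and the three stratification factors are not placed in it. If they are left out, the result is conservative: for an assumed stratum R² of 5% to 20% and 30% random dropout, an SE about 2% to 8% too large, type I error about 4.8% to 3.4%, and at most about 3 points of power lost. At the planned size, power stays above 90% either way. If the strata explain almost nothing, the loss vanishes. If the rule is used instead, the cost is a discretionary primary model, not an inflated error rate. No bias and no false-positive risk is shown, so this is a free improvement and not a must-fix.

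**What to change.** Replace the covariate sentence under Primary analysis with wording to this effect: the primary ANCOVA of 3-month CAPS contains treatment, sex, age group (<40 or ≥40 years) and sense of life threat; any further baseline covariate is named before outcome data are examined; models that add factors found to be prognostic are sensitivity analyses. Further covariates, such as the Peritraumatic Distress Inventory score, are a matter of preference and are not needed to settle this point.

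The three variables are already collected for the randomization. The cost is one sentence before code break, with no new data and no change to the sample size.

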#### Exploratory analysis

To complement the primary analyses, additional evaluation of secondary outcomes and sub-groups will be analyzed. The analysis will be exploratory, thus multiplicity will not be controlled. Evaluation with regression models in repeated measures as a mixed effect model will be conducted. Sensitivity analysis and imputed methods to missing variables will be used to examine the validity of the findings.

#### Estimation of sample size

Forty-nine cases are required, given that the expected CAP score difference between the groups at 3 months is set as 10, with an α level of 0.05 (two-tailed), a β level of .10, and standard deviation of 15. Discontinuation and dropout are estimated to be around 30% of the participants, indicating that 70 cases are needed. Thus, the desired number of participants in each group is 70, with a total of 140 cases. However, if this trial becomes difficult to continue due to finances, man-power, or physical factors, there is a possibility that the accumulation of cases will be stopped before the desired number is achieved.

#### Time periods of the study

Study period: December 2008 through December 2013

Enrollment period: December 2008 through June 2013

Follow-up period: December 2008 through December 2013

### Ethical considerations

The present study protects the rights and welfare of participants in the spirit of ethical guidelines outlined under the Declaration of Helsinki. The study further respects the ethical principles of the Ministry of Health, Labour, and Welfare of Japan. Confidence is assured in the ethics, safety, scientific rigor, and reliability of the research. Personal information obtained in the course of the research is strictly secured to avoid external leaks. No special compensation is paid in the event of health damage directly related to the research. The research plan (2007–12) was deliberated upon and approved by the Ethics Committee of the National Disaster Medical Center on February 8, 2008.

### Criteria for discontinuing intervention, evaluation, and follow-up

The criteria for discontinuing intervention, evaluation, and follow-up with participants are set as follows.

#### Discontinuing intervention

Investigators discontinue the intervention if the participant refuses to continue the treatment with the test capsules or placebo, or if further intervention is difficult because concomitant drug administration is required medically. Investigators ask the participant whether he or she can participate in later evaluations and follow-up. The process for discontinuing registration is initiated and reasons for the discontinuation are fully reported. Later evaluations and follow-up are conducted as designed.

#### Discontinuing evaluation

Psychiatric evaluation is discontinued if a participant refuses to undergo evaluation. Investigators ask the participants whether they can participate in later evaluations and follow-up. The process for discontinuing registration is initiated and reasons for the discontinuation are fully reported. Later evaluations and follow-up are conducted as designed.

#### Discontinuing follow-up

Study participation is discontinued if a participant refuses to be followed up. Investigators undertake the process of discontinuing registration for follow-up and record the relevant details. Later evaluations and follow-up are not conducted.

#### Retraction of consent

When a participant retracts his or her consent, all intervention, evaluation, and follow-up is discontinued.

#### Deviation from the study protocol

When a participant deviates from the study protocol as noted in the following, a follow-up session is conducted as far as is possible: 1) capsules are not supplied or taken as scheduled, 2) documents necessary for evaluation are missing, and 3) continuing intervention is deemed difficult by the investigators for other reasons. Reasons for the deviation are recorded.

#### Discontinuation of the study

The study is discontinued in the event of any of the following.

1. The Data and Safety Monitoring Board recommends discontinuation of the study.

2. Serious adverse events and side-effects occur that make continuing the study difficult, and the Board recommends discontinuation of the study.

3. The principal investigator decides to discontinue the study.

### Data and safety monitoring

The data manager provides a report using a pre-determined template to the principal investigator and the Data and Safety Monitoring Board on a regular basis (once every 6 to 12 months). The Data and Safety Monitoring Board consists of the following three professionals with experience in clinical trials, who are not involved in this trial: [name] (critical care medicine), [name] (regulatory science), and [name] (psychopharmacology). The statistical analysis manager reviews the reports filed by the data manager in advance. Contents of the template include the following.

1. Study progress with case registration

2. Status of psychiatric evaluations and relevant issues

3. Occurrence of adverse events

4. Discussion of other relevant issues, problematic cases, and events

### Revision of the research plan and change of processes

The principal investigator will summon or e-mail investigators to discuss possible revisions to the research plan when the regular monitoring report indicates the presence of serious adverse events or events that may affect continuation of the study, thus suggesting safety problems in the study.

### Data access and responsibility

Drs. [name] and [name] have full access to all of the data in the study and take responsibility for the integrity of the data and the accuracy of analysis.

### Presentation of the trial results

The findings will be presented in medical journals and at academic conferences. The founding body will also be notified of the results. An application for a press release at the Press Club will be initiated if significant research results are obtained and the study is accepted for publication by an influential academic journal. Mainly the principal investigator is the corresponding author in all presentations, and the first author and co-authors will be determined according to their intellectual contributions. In addition, individuals who join the study after it was approved and work fully toward the implementation and progress of the study may obtain authorship with the approval of the principal investigator.

## Discussion

It is suggested that hippocampal neurogenesis may play an important role in the periodic clearance of hippocampal memory traces in contextual fear conditioning [36]. Thus, hippocampal neurogenesis is emerging as a possible mediator of the effect of omega-3 fatty acids on fear memory. Modulating adult hippocampal neurogenesis by omega-3 fatty acid supplementation may well then be a good target for the prevention of PTSD. Intervention with omega-3 fatty acid appears acceptable in broad clinical practice because of its convenience, empirical results in animal studies, and much less serious side effects than any psychotherapeutic drugs.

The TPOP study is designed to evaluate the efficacy of omega-3 fatty acid supplementation for PTSD prevention among injured patients. The open trial [38] provided promising support for our hypothesis: omega-3 fatty acid supplementation significantly attenuated PTSD symptoms at 3 months as a primary outcome, as compared with the hypothetical mean. We believe the results of the TPOP will be of importance: accidental injury occurs across the globe and omega-3 fatty acid supplementation, if found to be efficacious for preventing PTSD, could maintain the mental health of the injured.

## Abbreviations

BAQ: Buss-Perry Aggression Questionnaire; BDNF: Brain-derived neurotrophic factor; CAPS: Clinician-Administered PTSD Scale; CD-RISC: Connor-Davidson Resilience Scale; DHA: Docosahexaenoic acid; EPA: Eicosapentaenoic acid; FFQ: Food Frequency Questionnaire; HADS: Hospital Anxiety and Depression Scale; ICU: Intensive care unit;IES-R: Impact of Event Scale-Revised; MADRS: Montgomery-Asberg Depression Rating Scale; MDD: Major depressive disorder; MINI: Mini International Neuropsychiatric Interview; MVA: Motor vehicle accident;PTSD: Posttraumatic stress disorder; SF-36: The 36-item short form of the MOS Questionnaire; TPOP: Tachikawa Project for Prevention of PTSD with Polyunsaturated Fatty Acid
